**Table 3. Diagnostic Criteria for Myalgic Encephalomyelitis/Chronic Fatigue Syndrome**

| Patients must have all four criteria:   1. A substantial reduction or impairment in the ability to engage in pre-illness levels of activity (occupational, educational, social, or personal life) that: a) lasts for more than 6 months, and b) is accompanied by fatigue that is often profound, of new onset (not lifelong), not the result of ongoing or unusual excessive exertion, and not substantially alleviated by rest. 2. Post-exertional malaise (defined as worsening of symptoms after physical, mental or emotional exertion that would not have caused a problem before the illness). 3. Unrefreshing sleep (defined as not feeling better or less tired even after a full night of sleep despite the absence of specific, objective sleep alterations). 4. At least one of the following two symptoms:    1. Cognitive impairment (defined as problems with thinking, memory, executive function, and information processing, as well as attention deficit and impaired psychomotor functions. These can be exacerbated by exertion, effort, prolonged upright posture, stress, or time pressure, and may have serious consequences on a patient’s ability to maintain a job or attend school full time).    2. Orthostatic intolerance (defined as a worsening of symptoms upon assuming and maintaining upright posture as measured by objective heart rate and blood pressure abnormalities during standing, bedside orthostatic vital signs, or head-up tilt testing. Orthostatic symptoms can include lightheadedness, fainting, increased fatigue, cognitive worsening, headaches, or nausea that are worsened with upright posture (either standing or sitting) during day-to-day life and are improved (though not necessarily fully resolved) with lying down). |
| --- |

## 3.6. Data collection

### 3.6.1. Trial procedures and evaluations

Results for a SARS-CoV-2 viral test (i.e., nucleic acid amplification test or antigen test) are confirmed by the research staff either through visualizing the result in the EMR or by reviewing an image of the test result sent to the research staff by the participant. After an eligible patient enrolls in the study, a combination of self-reported information and information generated from the patient’s own health information is connected to the Hugo platform, collected, and sent to the study site over the 18-month follow-up period (Appendix A).

Self-reported data: Using Hugo, surveys including the variables outlined above are sent by electronic mail or text to participants at the research site every 3 months throughout the follow-up period. These responses are sent through the Hugo platform and then shared with the study team. Subjects use their personal smartphone, tablet, computer, or other electronic device to connect to the internet and answer surveys that ascertain their symptoms, health care use, health care experience, and physical, mental, and social health over an 18-month period. Responses sent by participants are encrypted. To minimize participant burden, each data collection episode is designed to take approximately 15 minutes or less to complete.

Patient-Centric Data Sharing: Participants connect their own health system portal account with the Hugo platform at enrollment (Figure 1). Hugo is a web-based platform used to longitudinally collect data for this study. The Hugo platform gives patients the ability to collect and maintain their personal health records in a centralized, cloud-based account. Participants will create a Hugo account and connect the health system portal accounts they choose to connect with the Hugo platform. This may include patient portals from healthcare systems, pharmacies, laboratories, and insurers. Individuals direct Hugo to share their health records with the research team according to the terms in the informed consent. This information is sent from Hugo to the research analytic core and stored in accordance with their institutional policies. The specific portal-related information available through Hugo in use for INSPIRE includes hospital and clinical patient portals yielding current data on medications, appointments and visits, test orders and results, clinical notes, problems, diagnoses, vital signs, demographics, and immunizations. After the study, participants can maintain their Hugo account or opt to delete their account and data.

Participants can connect their health system(s) portal accounts with Hugo at set up but may need assistance if they have technical issues or if they do not complete this initial step at enrollment. Once participants create an account in Hugo and link their portals, no additional actions are required to stream data into Hugo. Technical support from the enrolling site or clinical core is provided to resolve any difficulties setting up an account.

During the study, periodically Hugo downloads identifiable data outlined in the IRB protocol and consent form. Research sites have access to site-specific dashboards to track enrollment, identify which data sources are connected, and to monitor survey responses. Deidentified, individual-level data are sent from Hugo to the analytic team periodically for quality assurance and analysis.

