# 2. INTRODUCTION

## 2.1. Background and rationale

The COVID-19 pandemic is associated with considerable morbidity and mortality. As of May 2021, > 32.6 million COVID-19 cases and > 580,000 attributed deaths have been detected in the USA [[1]](https://www.spiritprotocol.com/api/docx/https://paperpile.com/c/nKRweq/D7DYc). Globally, > 160 million COVID-19 cases and > 3.3 million attributed deaths have been reported [[2]](https://www.spiritprotocol.com/api/docx/https://paperpile.com/c/nKRweq/0puKg). The clinical course of acute COVID-19 is well-described [[3–7]](https://www.spiritprotocol.com/api/docx/https://paperpile.com/c/nKRweq/lU1D+t8iR+K9mW+Mq1f+OJ8y). Post-acute COVID-19 is defined as persistence of symptoms or development of sequelae after 3 or 4 weeks from the onset of acute symptoms of COVID-19 [[8–10]](https://www.spiritprotocol.com/api/docx/https://paperpile.com/c/nKRweq/XHsQi+bmgL6+etRcB). This definition is further divided into subacute or ongoing symptomatic COVID-19, including symptoms from 4-12 weeks beyond acute COVID-19, and a chronic or post-COVID-19 syndrome, which includes symptoms persisting or present beyond 12 weeks of acute COVID-19 not attributable to alternative diagnoses [[8,11]](https://www.spiritprotocol.com/api/docx/https://paperpile.com/c/nKRweq/XHsQi+1Igm8). Information on post-acute COVID-19 and long-term sequelae of SARS-CoV-2 infection is only recently emerging [[12–15]](https://www.spiritprotocol.com/api/docx/https://paperpile.com/c/nKRweq/DBuqU+NqrkR+3wwBG+PRH0f).

To characterize post-COVID-19 syndromes better, there is an urgent need for broader representation in study population selection to allow for representativeness and generalizability, to set objective outcomes that are not limited to symptoms but include illness events and clinical events, and to include SARS-CoV-2 negative individuals to ensure other effects of the pandemic are considered in the analysis (e.g. impact on livelihoods, mental health, food security, and mobility) [[16]](https://www.spiritprotocol.com/api/docx/https://paperpile.com/c/nKRweq/38UeS). Such work will help clinicians know what post-infectious sequelae to expect and who is at increased risk, will help ensure research findings can be compared across studies, and will move us towards addressing critical health care response needs.

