## 2.2. Objectives

Our objectives are to understand the medium- and long-term sequelae of symptomatic SARS-CoV-2 infection, to describe predictors of sequelae as reported by individuals and as recorded in their EMR, and to assess the intersection of long-term sequelae of COVID-19 with other previously defined syndromes with overlapping features such as myalgic encephalomyelitis/chronic fatigue syndrome (ME/CFS).

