**Table 1: Inclusion and exclusion criteria**

Inclusion criteria:

1. Fluent in English or Spanish
2. Age 18 years or older
3. Self-reported symptom suggestive of acute SARS-CoV-2 infection [[19]](https://www.spiritprotocol.com/api/docx/https://paperpile.com/c/nKRweq/KvIKQ)
4. Tested for SARS-CoV-2 with any FDA-approved or authorized viral test (i.e., nucleic acid amplification test or antigen test [[20]](https://www.spiritprotocol.com/api/docx/https://paperpile.com/c/nKRweq/mGkhJ)) within 42 days of enrollment

Exclusion criteria:

1. Unable to provide informed consent
2. Study team unable to confirm the result of a diagnostic test for SARS-CoV-2
3. Does not have access to a hand-held device or computer that would allow for digital participation in the study
4. Lawfully imprisoned while participating in the study

**Table 2: COVID-19 clinical criteria case definition (August 2020)** [[18]](https://www.spiritprotocol.com/api/docx/https://paperpile.com/c/nKRweq/MqHQg)

*In the absence of a more likely diagnosis,*

At least TWO of the following symptoms:

- Fever (measured or subjective)
- Chills
- Rigors
- Myalgia
- Headache
- Sore throat
- Nausea or vomiting
- Diarrhea
- Fatigue
- Congestion or runny nose

Or any ONE of the following symptoms:

- Cough
- Shortness of breath
- Difficulty breathing
- New olfactory disorder
- New taste disorder

Or severe respiratory illness with at least ONE of the following:

- Clinical or radiographic evidence of pneumonia
- Acute respiratory distress syndrome (ARDS)

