## 3.3. Recruitment

Participant Identification and Enrollment

Methods used to recruit potentially eligible participants vary by site, although each site applies the same eligibility criteria described in Table 1. Most sites screen for eligible participants among those tested for SARS-CoV-2 infection. With this process in place, we seek to enroll participants as close to their initial date of SARS-CoV-2 testing as possible. Identification and enrollment methods include: i) a member of the study team accesses the EMR to screen for potentially eligible individuals based on SARS-CoV-2 testing and reason for testing and contact eligible individuals, ii) participants learn of the study from a poster, brochure, or social media and can enroll directly through the online portal, iii) research staff reach out to potentially eligible individuals in-person, over the phone, or by text or e-mail to offer and facilitate enrollment (e.g., contact information obtained from organizations including city and state agencies conducting SARS-CoV-2 testing). The method or combinations of methods used at each site are based on local IRB approval and practical considerations. Though minor differences exist across sites, the study eligibility criteria, online enrollment, and data collection methods are identical, which allows for compilation and comparison of data across sites.

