## 3.14. Participant timeline

Figure 1. Participant Timeline

|  | Enrolment | Post-enrollment |  |  |  |  |  | Close-out |
| --- | --- | --- | --- | --- | --- | --- | --- | --- |
| TIMEPOINT | 0 | 3 mos. | 6 mos. | 9 mos. | 12 mos. | 15 mos. | 18 mos. | tx |
| ENROLLMENT: |  |  |  |  |  |  |  |  |
| Eligibility screen | X |  |  |  |  |  |  |  |
| Informed consent | X |  |  |  |  |  |  |  |
| ASSESSMENTS: |  |  |  |  |  |  |  |  |
| Age, gender, symptoms of SARS-COV-2 infection, recent health care use, social determinants of health | X |  |  |  |  |  |  |  |
| Outpatient visit, emergency department visit, hospitalization, intensive care stay, death, physical and mental health (PROMIS-29), cognitive SF-8, hospital-free survival, intensive care-free survival, dyspnea, cough, exercise, social determinants of health, work and activity status, myalgic encephalomyelitis/chronic fatigue syndrome |  | X | X | X | X | X | X | X |
| Preexisting conditions |  | X | X | X | X |  |  | X |

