## 3.17. Safety/harms

Study risks are related to invasion of privacy and potential breach in confidentiality. Data maintained at the research site will include minimum necessary information and will be secured according to institution standards. Data maintained by Hugo Health will be subject to their privacy security policies https://hugo.health/security), Privacy Notice (https://hugo.health/privacy-notice), Terms of Service (https://hugo.health/terms-of-service/). Participants may experience inconvenience of filling out electronic patient-reported outcome measure surveys, which should take up to 20 minutes for the longer surveys (at enrollment baseline), and 15 minutes for the weekly/monthly surveys.

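### Outcome surveys run on an enrolment clock while enrolment may be up to 42 days after the test, so each nominal visit spans 6 weeks of time since test; the protocol also contradicts itself on which surveys are sent before 3 months

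*Protocol*

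**What the plan says.** **Eligibility window.** Table 1 (section 3.2) requires a viral test "within 42 days of enrollment". Section 3.3 adds an intention, not a limit: "we seek to enroll participants as close to their initial date of SARS-CoV-2 testing as possible".

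**Survey clock.** Section 3.6.1 states: "surveys including the variables outlined above are sent by electronic mail or text to participants at the research site every 3 months throughout the follow-up". It gives 18 months as the length of follow-up. The timeline in section 3.14 has the header "TIMEPOINT | 0 | 3 mos. | 6 mos. | 9 mos. | 12 mos. | 15 mos. | 18 mos. | tx", with column 0 labelled as enrolment. Its outcome row (PROMIS-29, cognition, dyspnea, cough, work status, ME/CFS, utilisation) is empty at 0 and marked from 3 months on. At 0 it marks demographics, acute symptoms, recent care use and social determinants. No visit is tied to the test date or to symptom onset.

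**Illness phases.** Section 2.1 dates post-acute COVID-19 from symptom onset and divides it into "subacute or ongoing symptomatic COVID-19, including symptoms from 4-12 weeks beyond acute COVID-19" and a chronic phase beyond 12 weeks. Section 2.2 states: "Our objectives are to understand the medium- and long-term sequelae of symptomatic SARS-CoV-2 infection". Medium-term is not defined in weeks.

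**Statements that do not fit the timeline.** Section 3.17 describes participant burden as "15 minutes for the weekly/monthly surveys", after mentioning longer surveys at enrolment. Section 3.9.1 plans to compare health status at baseline as well as at follow-up.

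**Adjustment.** The patient-level factors listed in section 3.9.1 are age, sex, race/ethnicity, income and underlying conditions. Test-to-enrolment lag is not among them.

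**The concern.** The study asks what happens over time after an infection, but its visits are counted from the day a participant joined. Two people answering the same 3-month survey can be 6 weeks apart in time since their test. If test-positive and test-negative participants differ in how soon after testing they join, a comparison at a nominal visit compares them at different times since illness. Section 3.3 says recruitment methods vary by site, so lag may well vary; nothing in the protocol shows that it varies by test result.

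The ME/CFS outcome is where the clock meets a threshold in the document. Table 3 requires impairment lasting more than 6 months, so the chance of meeting the duration criterion at the 6-month survey depends partly on enrolment lag.

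The schedule also leaves a gap before 3 months in the main patient-reported measures. The protocol is not consistent on whether that gap exists, so a reader cannot tell what the earliest patient-reported result will be.

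**Working it through.** **Inputs**
- Test-to-enrolment lag L: 0 to 42 days (Table 1).
- Outcome surveys every 3 months for 18 months, counted from enrolment (sections 3.6.1 and 3.14).
- Phase limits: 4 and 12 weeks (section 2.1).
- ME/CFS duration: more than 6 months (Table 3).
- Month length: 365.25/12 = 30.44 days.

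**Plan's own schedule reproduced.** 18/3 = 6 surveys, matching the six post-enrolment columns in section 3.14.

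**Time since test.** Weeks = (visit month × 30.44 + L)/7.

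| Visit | L = 0 | L = 42 |
|---|---|---|
| Enrolment | 0.0 | 6.0 |
| 3 months | 91.3/7 = 13.0 | 133.3/7 = 19.0 |
| 6 months | 182.6/7 = 26.1 | 224.6/7 = 32.1 |
| 12 months | 52.2 | 58.2 |
| 18 months | 78.3 | 84.3 |

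The spread is 42/7 = 6.0 weeks at every visit.

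**Source of the 4 to 12 week gap.** With L = 0 the first outcome survey is already at 13.0 weeks. The gap therefore comes from the 3-month first survey, and the lag only pushes it later. With 30-day months the range is 12.9 to 18.9 weeks. With 28-day months it is 12.0 to 18.0, which touches the limit without entering the window.

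**Counting from onset.** The protocol gives no onset-to-test interval. Assuming onset from 3 days after the test to 28 days before it, the first outcome survey falls at (91.3 + 0 − 3)/7 = 12.6 to (91.3 + 42 + 28)/7 = 23.0 weeks. The gap remains.

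**Counting from the end of the acute illness.** If the phase limits start after an acute illness of 2 to 4 weeks (an assumption), the first outcome survey falls at 11.0 to 17.0 weeks (2 weeks subtracted) or 9.0 to 15.0 weeks (4 weeks subtracted). It then reaches the end of the window for earlier enrollees.

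**ME/CFS threshold.** Six months is 182.6/7 = 26.1 weeks. Using the test date as a stand-in for the start of impairment, the 6-month survey is 0 weeks past the threshold for a day-0 enrollee and 6.0 weeks past it for a day-42 enrollee.

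**If the monthly surveys in section 3.17 exist.** The first two would fall at 30.44/7 = 4.3 to 72.44/7 = 10.3 weeks, and at 60.9/7 = 8.7 to 102.9/7 = 14.7 weeks after the test. They would largely fill the gap.

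**Recall.** Section 3.5 gives PROMIS a seven-day look-back, except for physical function and social roles, which state none. A seven-day look-back at 13 weeks does not reach back to week 12 or earlier; 13.0 − 1 = 12.0.

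**The case against.** The strongest reply is that the schedule is a reasonable choice for a low-burden online cohort, that sites aim to enrol close to testing, and that the time axis and lag adjustment belong in an analysis plan that is not shown. Much of this stands. A 3-monthly schedule is defensible, and the analysis detail may be settled elsewhere. What the reply does not remove is that the protocol fixes an enrolment clock, lists its adjustment factors without lag, and gives statements about survey timing that cannot all be true.

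Four stronger readings are tempting, and the protocol does not support them:
- **The lag causes the gap in weeks 4 to 12.** It does not; the gap is there at zero lag, and moving the time origin would not close it.
- **The same visit covers different disease phases.** Counted from test or onset, every outcome survey lies beyond 12 weeks, in one protocol-defined phase. Phases differ at the 3-month visit only if weeks are counted after the acute illness, and then the gap is no longer complete.
- **The medium-term objective rests on medical records alone.** Medium-term is never equated with weeks 4 to 12. Section 3.5 collects utilisation and clinical events by self-report as well, and the enrolment symptom survey falls in weeks 4 to 6 for those who join on days 28 to 42. Recall periods other than that of PROMIS are in an appendix that is not shown.
- **The comparison is biased.** The protocol gives no lag distribution by test result and no recovery curve.

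It is also fair to say that an empty cell in the timeline is weak evidence on its own: pre-existing conditions are unmarked at enrolment too. That is a further reason to reconcile the sections.

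**Conclusion.** The point holds in a limited form. Each nominal outcome visit spans 6.0 weeks of time since test (13.0 to 19.0 at 3 months, 26.1 to 32.1 at 6 months). This is largest relative to elapsed time at the first survey, and most consequential at 6 months because of the ME/CFS duration criterion. On the timeline as drawn, no scheduled PROMIS, cognition or ME/CFS survey falls in weeks 4 to 12 from test or onset; this rests on the timeline being complete and on that reading of the phases.

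Two inconsistencies stand on any reading: section 3.17 against sections 3.6.1 and 3.14 on survey frequency, and section 3.9.1 against section 3.14 on baseline health status. The 6-week figure is the maximum that eligibility permits. The actual spread depends on the lag distribution, which the protocol does not give. Differential lag between the groups is a risk to guard against, not a demonstrated bias.

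**What to change.** 1. **Time axis and lag.** Analyse and report outcomes by time since the index test date, or since symptom onset where recorded, and add test-to-enrolment lag to the adjustment factors in section 3.9.1. Within a single nominal visit, scheduled time since test is lag plus a constant, so one of the two terms suffices there; in a model pooling visits both can be fitted. Report the lag distribution by test result.
2. **Sensitivity analysis in early enrollees.** The cut-off is the team's choice. Limiting to lags of 0 to 14 days narrows the 3-month visit to 13.0 to 15.0 weeks, and 0 to 28 days to 13.0 to 17.0 weeks.
3. **Reconcile sections 3.6.1, 3.9.1, 3.14 and 3.17** on which surveys are sent, with what content, and when, including whether health status is measured at enrolment. If no patient-reported outcome survey exists before 3 months, state that patient-reported sequelae are assessed from about 13 weeks after the test onward.

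Items 1 and 2 cost slightly more analysis work. The test date is needed anyway to apply the 42-day criterion; an onset date is not listed in the timeline, so the test date is the safe default. Item 3 is text. An additional early survey is optional: it would fill the gap at the price of participant burden, which section 3.6.1 sets out to limit.

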## 3.7. Human subjects considerations

Participants are eligible to receive a small incentive for completion of each periodic questionnaire; the total value will be $100 over the course of the study. Researchers will not provide any information gathered through the study to clinicians engaged in treating the patient. Patients will be informed and reminded that their responses will not be provided to their healthcare team, both at the beginning of the study during the consent process and throughout the study on the regular questionnaires.

## 3.8. Sample size

Our target enrollment is 3,600 people with SARS-CoV-2 infection confirmed by a positive SARS-CoV-2 viral test (i.e., nucleic acid amplification test or antigen test) and 1,200 people with a negative SARS-CoV-2 viral test. We expect that the age distribution of enrolled subjects will represent that of patients tested in each site. Four of the sites (Yale, Jefferson, Rush and UW) draw on smaller catchment populations so have planned enrollment of 400 subjects per site (300 individuals with SARS-CoV-2 and 100 individuals without SARS-CoV-2). Four sites (UT Southwestern, UT Houston, University of California, San Francisco, and University of California, Los Angeles) have larger catchment populations so have planned enrollment of 800 subjects per site (600 individuals with SARS-CoV-2 and 200 individuals without SARS-CoV-2).

We estimated the power to detect relative differences in outcome rates between those who are symptomatic and test positive for SARS-CoV-2 as compared to those who are symptomatic but test negative for SARS-CoV-2. These power calculations are agnostic to the outcome of interest but based on the aim to examine relative differences in long-term outcomes between individuals with and without SARS-CoV-2 based on and between age strata. For comparison of ME/CFS incidence in SARS-CoV-2 infected vs uninfected, power calculations are based on the null hypothesis that there is no difference between individuals with and without SARS-CoV-2 in the outcome rate.

The assumptions used to generate these power calculations include both elements outside the study’s team’s control (e.g., baseline outcome rate in individuals without SARS-CoV-2) as well as elements amenable to changes in study design (e.g., individuals with SARS-CoV-2 strata group size).  Assumptions include:

- 3,600 individuals with SARS-CoV-2 and 1,200 individuals without SARS-CoV-2
- Baseline outcome rate in individuals without SARS-CoV-2: 2.5% with the contingency that the baseline outcome rate may vary between age strata (18-40 years, 41-64 years, ≥ 65 years)
- Outcome rate in individuals with SARS-CoV-2: presented as scenarios based on absolute or relative differences from baseline outcome rate in individuals without SARS-CoV-2. Also presented under the likely scenario that outcome rates vary between age strata
- Alpha = 0.05 (fixed)

Under conservative assumptions, the planned sample has 97.8% power to detect an absolute outcome rate difference of 2.5% between individuals with versus without SARS-CoV-2 infection. The power to detect a relative difference in outcome rates is highly sensitive to both the actual baseline outcome rate as well as variation in baseline outcome rates between age strata. The study would have adequate power (conventionally defined as 0.8) to detect a difference as small as 5% in outcomes with 1,224 total participants (25.5% of total planned enrollment) enrolled in a 3:1 ratio, or 918 COVID+ and 306 COVID negative (Table 4).

